### Sample size

We will enrol 124 patients and randomise them in a two-stage process. First, a 1:1 randomisation will assign patients to low-dose morphine or pregabalin (62 per group). Within each arm, a second independent 1:1 randomisation will assign patients to CCT or no CCT. This will result in four groups of 31 patients each. We powered the study on the 62-patient comparisons (ie, morphine vs pregabalin; CCT vs no CCT) rather than on individual groups. Because we anticipate a smaller effect size for the morphine versus pregabalin contrast, we conservatively based our sample size on this comparison.

The primary outcome is the change from baseline in natural log-transformed 24-hour cough frequency at 6 weeks. Assuming a 30% relative reduction in 24-hour cough frequency^31^ (corresponding to a mean difference of −0.357 units on the log scale), an SD in log coughs/hour of 0.6,^32^ and a 10% dropout, a total sample size of 124 participants (62 per intervention comparison) will provide 80% power at a two-sided alpha of 0.025. To maintain a family-wise type I error rate of 5% across our two co-primary hypotheses (morphine vs pregabalin and CCT vs no CCT), we applied a Bonferroni correction and set the significance level at α=0.025 for each comparison. We performed these calculations using the pwr.t.test function in the pwr package in R studio V.4.3.1 (Posit Software, PBC; Boston, MA, USA).

While our primary interest lies in estimating main effects, the factorial design also permits exploration of potential interactions between treatments. For the sample size calculation, we assumed no significant interaction—that is, that the effect of one intervention is consistent across levels of the other. Under this assumption, we will estimate the effect of morphine versus pregabalin by averaging across CCT and no CCT arms, and the effect of CCT versus no CCT by averaging across morphine and pregabalin arms.

To ensure sufficient participant enrolment, we will monitor recruitment at each site monthly and enact strategies (eg, additional sites) as needed to achieve the target sample size.

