### Primary analysis of the primary outcome at 6 weeks

For the primary outcome at 6 weeks, we will use a linear model to estimate changes from baseline in log-transformed 24-hour coughs per hour. The model will include treatment group, site and baseline log-transformed 24-hour cough frequency as fixed effects. Each primary hypothesis (morphine vs pregabalin; CCT vs no CCT) will be tested at a two-sided alpha of 0.025.

We will handle missing data under a missing-at-random assumption using multiple imputation. If ≥15% of outcome data are missing, we will perform a missing-not-at-random (MNAR) sensitivity analysis using a pattern-mixture model. Missing outcomes will be assumed to differ by a fixed offset (eg, 10%) from observed values, and the impact on treatment effects will be examined. Model assumptions (ie, normality, homoscedasticity) will be checked.

Mean changes from baseline in log-transformed 24-hour coughs per hour will be estimated as marginal means with their 95% CIs, and between-group differences (95% CI) will be calculated. To present geometric means of 24-hour coughs per hour for treatment groups at each time point, we will back transform the log-transformed estimates. The percent difference in the change from baseline and 6 weeks between treatment groups will be calculated as 100*(e^diff^−1), where diff represents the between-group difference on the log scale. P values for treatment effects at 6 weeks will be reported.

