### Sensitivity analyses

#### Testing the impact of protocol adherence

Anticipating that patients may discontinue treatment due to AEs, we will assess the robustness of the primary analysis at 6 weeks to deviations from the intervention protocol. This sensitivity analysis will occur with the primary outcome and select secondary outcomes in the per-protocol population.

For the morphine versus pregabalin comparison, the per-protocol population will include patients who received ≥80% of the intended study drug over the 6-week period. For the CCT versus no CCT comparison, the per-protocol population will include patients who (1) completed at least four out of the five weekly adherence diaries and (2) reported using at least one cough control strategy in three of those diary entries.

The same linear model or linear mixed-effects model described in the primary analysis will be applied to the per-protocol population.

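### The missing-not-at-random check would not run at the dropout the protocol plans for, and the example offset of 10% would barely stress the primary result if it did run

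*Protocol article*

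**What the plan says.** The protocol article, under Primary analysis of the primary outcome at 6 weeks, sets the main approach: "We will handle missing data under a missing-at-random assumption using multiple imputation". The departure from that assumption is conditional: "If ≥15% of outcome data are missing, we will perform a missing-not-at-random (MNAR) sensitivity analysis using a pattern-mixture model". The form of the departure follows: "Missing outcomes will be assumed to differ by a fixed offset (eg, 10%) from observed values". The same sentence says that the effect on the treatment comparison will be looked at. It gives no range of offsets, no statement on whether the offset may differ by arm, and no tipping point.

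Under Sample size, the calculation allows for dropout: "and a 10% dropout, a total sample size of 124 participants". Under Testing the impact of protocol adherence, the per-protocol analysis is motivated thus: "Anticipating that patients may discontinue treatment due to AEs". The sections on secondary outcomes and responder analyses at 6 weeks adopt the same handling of missing data, so the rule reaches beyond the primary outcome.

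**The concern.** A sensitivity analysis for missing data should show how far the missing outcomes must depart from MAR before the conclusion changes. Two features of the published rule work against that.

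- **The trigger.** It lies above the dropout that the protocol itself expects, and it appears to count missing outcomes over the whole trial. A marked imbalance between arms could therefore pass without any check.
- **The offset.** The only size mentioned is small. If the offset is the same in both arms, most of it cancels in the comparison.

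The trial is open-label. The two drugs have different expected side effects (Analysis of safety outcomes), and only one side of the second factor has five sessions and weekly diaries. Missingness related to both arm and outcome is therefore plausible. If the rule is followed as printed, either no check is reported or one is reported that could hardly have come out otherwise. Readers could take either as support for two co-primary conclusions.

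**Working it through.** **Inputs from the protocol (Sample size):** effect 0.357 on the log scale ("corresponding to a mean difference of −0.357 units on the log scale"); standard deviation 0.6 ("an SD in log coughs/hour of 0.6"); two-sided alpha 0.025 per comparison; 80% power; 62 against 62; 10% dropout. **Assumed:** the missing fractions by arm, shown as a range.

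**1. The plan's own figure.** d = 0.357 / 0.6 = 0.595. A two-sample t-test at two-sided 0.025 with 80% power needs 54.97, so 55 per side. 55 / 0.90 = 61.1, so 62 per side and 124 in total. The stated figure reproduces.

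**2. The trigger.** 10% of 124 is 12.4 missing outcomes. 15% of 124 is 18.6, so 18 missing (14.5%) triggers nothing. A split of 4 and 14 is 4/62 = 6.5% against 14/62 = 22.6%.

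**3. What a 10% offset does.** If missing values in arm A are shifted by δA and those in arm B by δB, the between-arm difference moves by

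shift = δA × mA − δB × mB,

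where m is the missing fraction. With δ = ln 1.1 = 0.095, the absolute shift is:

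| Missing, A / B | Same offset in both arms | Offset only in the arm with more missing (either arm if equal) |
|---|---|---|
| 10% / 10% | 0.000 | 0.0095 |
| 15% / 15% | 0.000 | 0.014 |
| 10% / 20% | 0.0095 | 0.019 |
| 5% / 25% | 0.019 | 0.024 |
| 0% / 30% | 0.029 | 0.029 |

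Taking 10% as a reduction (−ln 0.9 = 0.105) changes little: 0.105 × 0.30 = 0.032 in the last row.

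**4. The yardstick.** SE = 0.6 × √(2 / n observed per arm), ignoring the gain from baseline adjustment. At 10% missing, n = 55.8 and SE = 0.114. At 15%, n = 52.7 and SE = 0.117. The largest shift in the table is about 0.029 / 0.117 = 0.25 SE. The one-arm shift at 15% per arm is 0.014 / 0.117 = 0.12 SE.

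**5. How large a departure would matter.** The smallest significant difference is the t quantile at 0.9875 times the SE. The margin is 0.357 minus that difference, and the one-arm tipping offset is the margin divided by the missing fraction in that arm. The SE is treated as unchanged by the offset.

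| Missing | Smallest significant difference | Margin at 0.357 | One-arm tipping offset (log) | Cough frequency ratio |
|---|---|---|---|---|
| 10% per arm | 0.258 | 0.099 | 0.99 | 2.7 |
| 15% per arm | 0.266 | 0.091 | 0.61 | 1.84 |
| 20% per arm | 0.274 | 0.083 | 0.41 | 1.51 |
| 4 / 14 patients, offset in the arm with 14 | 0.266 | 0.091 | 0.091 / 0.226 = 0.40 | about 1.5 |

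For the last row, SE = 0.6 × √(1/58 + 1/48) = 0.117. In that case missing patients with about 50% higher cough frequency than imputed would overturn a planned-size result, and no check would have been run.

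An observed effect smaller than planned tips sooner. At 0.30 (assumed) and 10% missing per arm, the margin is 0.300 − 0.258 = 0.042 and the tipping offset 0.042 / 0.10 = 0.42, a ratio of about 1.5.

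**The case against.** The strongest reply has four parts.

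- **The offset need not be common.** A reader might infer that one identical offset is prescribed for both arms and that the check therefore cancels by construction. The text does not say so. Fixed may simply mean set in advance, and the 10% is given as an example. This stands, and the point does not rest on the common reading: at 10%, a one-arm offset also moves the difference by only about 0.014 at 15% missing per arm.
- **The detail may be elsewhere.** The article points to a supplementary summary of the analysis plan that is not shown, and a grid of offsets is something an article may leave to it. This stands for the range and for arm-specific values. It does not cover the trigger, which the article states outright and which conflicts in purpose with the planned dropout.
- **Stopping treatment is not the same as a missing outcome.** A reader might take the expected discontinuation for adverse events as expected missing data. The section on participant withdrawal strongly encourages follow-up after treatment stops and keeps compensation in place, and the analysis is by intention to treat. This stands and lessens the threat. It does not remove it, since the protocol still budgets for dropout.
- **The planned scenario is fairly robust anyway.** At 10% missing per arm and an effect of 0.357, the one-arm offset must reach about 1 log unit before significance is lost. This also stands, but only for an effect of the planned size and balanced missingness.

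**Conclusion.** The point holds in a limited form. At the planned 10% dropout the MNAR analysis is not run, and an imbalance as large as 4 against 14 missing outcomes would not set it off if the trigger is counted over the whole trial. When it does run at the example size, it moves the treatment difference by between 0 and about 0.03 log units, at most about a quarter of a standard error, under either reading of the offset and for the missing fractions considered.

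It would go too far to say that the check cannot test anything or that the primary result is unsafe. A common offset does move the estimate slightly when dropout is unequal, the size of the offset is left open, and a planned-size effect with 10% missing per arm withstands a large departure from MAR. The exact statement is that the published rule barely tests the assumption. The figures assume the protocol's SD of 0.6, no gain from baseline adjustment, and hypothetical missing fractions. This is an improvement that should be made, not a flaw that invalidates the design.

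**What to change.** In Primary analysis of the primary outcome at 6 weeks:

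1. Remove the 15% condition, so that the MNAR analysis is reported whatever the amount of missing data.
2. After imputation under MAR, add an offset on the log scale that varies separately in each arm of each factor (morphine and pregabalin; CCT and no CCT), including an offset in one arm only. Prespecify the range, for example 0 to ln 2, and extend it until the conclusion changes. The extension matters: at 10% missing per arm, a one-arm offset of ln 2 shifts the difference by only 0.693 × 0.10 = 0.069, short of the 0.099 margin at the planned effect.
3. Report the tipping point for each co-primary comparison, with the number missing by arm.
4. If the supplementary plan already allows arm-specific offsets, say so in the protocol text and align the two.

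The cost is a sentence or two and a short loop around the multiple imputation already planned, with no new data and no change to sample size. The range should be fixed before any outcome data are seen, since offsets chosen afterwards would carry little weight.

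### The two primary contrasts are tested at two-sided 0.025 but reported with 95% confidence intervals, which correspond to a 0.05 test

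*Protocol article*

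**What the plan says.** Under Sample size, the protocol article states the error target and the method: "To maintain a family-wise type I error rate of 5% across our two co-primary hypotheses", followed by "we applied a Bonferroni correction and set the significance level at α=0.025 for each comparison". The trial is sized at that level: "a total sample size of 124 participants (62 per intervention comparison) will provide 80% power at a two-sided alpha of 0.025".

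Under Primary analysis of the primary outcome at 6 weeks, the test level is repeated: "Each primary hypothesis (morphine vs pregabalin; CCT vs no CCT) will be tested at a two-sided alpha of 0.025". The same section sets the interval for those contrasts: "between-group differences (95% CI) will be calculated". It also says that p values will be reported. It does not say that the 95% intervals are unadjusted, or that they play no part in deciding significance.

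For the secondary outcomes, the next section uses 0.05 with 95% intervals, so test and interval agree there. The mismatch concerns the primary outcome only.

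**The concern.** A two-sided test at level α and a confidence interval at level 1 − α give the same answer: the test rejects exactly when the interval excludes no effect. A test at 0.025 therefore pairs with a 97.5% interval. With a 95% interval, any result with p between 0.025 and 0.05 is declared non-significant beside an interval that excludes zero on the log scale (0% after back-transformation).

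This falls on the two results for which the trial took on multiplicity control and sized itself accordingly. In the discordant range, an abstract giving the estimate and its 95% interval would look positive although the pre-specified rule says it is not. Nor do the two headline intervals together carry the 95% confidence that a 5% family-wise error implies.

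**Working it through.** **Inputs** (Sample size section): log-scale difference 0.357 ("corresponding to a mean difference of −0.357 units on the log scale"), SD 0.6 ("an SD in log coughs/hour of 0.6"), 10% dropout, 62 per side, two-sided α = 0.025 per comparison, two-sample t-test.

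**1. Reproducing the sample size.** With the noncentral t distribution, 55 per side gives 80.0% power at 0.025. Then 55 / 0.90 = 61.1, rounded up to 62 per side, or 124 in total. The stated figure reproduces exactly.

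**2. Power at the two levels.** Evaluable per side: 62 × 0.90 = 55.8. Standard error: 0.6 × √(2/55.8) = 0.1136.
- Power at 0.025: 80.7%
- Power at 0.05: 87.6%
- Chance that p lies between 0.025 and 0.05 at the design effect: 87.6% − 80.7% = 6.9% per comparison
- The same chance under the null: 5% − 2.5% = 2.5% per comparison

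**3. Where the discordant zone lies.** The t multipliers (109.6 df) are 1.982 for 95% and 2.273 for 97.5%.
- 95% half-width: 1.982 × 0.1136 = 0.225, so the interval excludes no effect once the observed reduction exceeds 1 − e^(−0.225) = 20.2%
- 97.5% half-width: 2.273 × 0.1136 = 0.258, so the 0.025 test rejects once it exceeds 1 − e^(−0.258) = 22.8%
- Observed reductions between about 20.2% and 22.8% are discordant
- Ratio of widths: 2.273 / 1.982 = 1.147, so the matching interval is 14.7% wider

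**4. Joint behaviour of the two intervals** (taken as independent).
- Two 95% intervals: 0.95² = 90.25% joint coverage. Read as tests, their family-wise error would be 1 − 0.9025 = 9.75%.
- The planned tests at 0.025: 1 − 0.975² = 4.94%

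**5. Holm, as a separate question.** The smaller p is tested at 0.025 and, if it is significant, the other at 0.05. With independent tests, power for one comparison = P(p₁ ≤ 0.025) + P(0.025 < p₁ ≤ 0.05) × P(p₂ ≤ 0.025). For morphine versus pregabalin:
- CCT also gives 30%: 0.807 + 0.069 × 0.807 = 86.3%
- CCT almost certain to be detected: 0.807 + 0.069 = 87.6%, the ceiling
- CCT has no effect: 0.807 + 0.069 × 0.025 = 80.8%, a gain of about 0.2 points

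Power to reject both, with equal effects, rises from 0.807² = 65.1% to 76.3%. Power to reject at least one stays at 96.3%. Family-wise error under the global null is about 4.95%, as for Bonferroni. With one true null and the other effect at 0.357 it is 0.025 + 0.025 × 0.807 = 4.5%, still below 5%.

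**The case against.** The decision rule is explicit: significance is judged at 0.025, and no sentence gives that role to the interval or claims joint 95% coverage. A 95% interval is a common reporting convention, and the discordant zone is narrow. A reader might infer from the mismatch that the trial's type I error is inflated. The document does not support that: the planned tests hold the family-wise error at 5%, and the 9.75% figure arises only if someone overrides the stated rule and reads the intervals as tests. All of this stands and limits the weight of the point. It does not remove it, because the article nowhere tells the reader that the headline intervals are unadjusted.

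A second tempting reading is that Bonferroni is itself a mistake that wastes power. That is not supported either. Bonferroni is valid, was specified in advance, and delivers the planned 80%. It also offers one fixed threshold and one matching interval per comparison. The gain from Holm depends on CCT, for which the protocol gives no planning effect; it says only that the drug contrast is expected to be the smaller of the two.

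Holm can also bring back the same kind of disagreement. A second-step rejection at 0.05 can sit beside a 97.5% interval that includes no effect. With Bonferroni and 97.5% intervals this cannot happen.

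The analysis plan summary in online supplemental file 5 is not at hand. A plan using 97.5% intervals would contradict the article's text rather than settle the matter.

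**Conclusion.** The mismatch is real and confined to reporting of the primary outcome: tests at 0.025, intervals at 95%. Error control of the planned tests is intact. The size is about a 6.9% chance per comparison of a failed test beside an interval excluding no effect at the design effect, 2.5% under the null, and joint coverage of about 90.25% instead of at least 95%.

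Holm is an optional gain in efficiency and corrects no error. It adds about 5.6 points of power for the drug contrast if both effects are 30%, at most about 7 points, and about 0.2 points if CCT does nothing.

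These figures assume SD 0.6, 10% dropout, no interaction, independent test statistics for the two factors, and no credit for baseline adjustment.

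**What to change.** **Needed.** Report 97.5% confidence intervals for the two primary between-group differences, and use the same level for any interval on the back-transformed percentage difference. If 95% intervals are also shown, label them as unadjusted and not decisive for significance. The cost is primary intervals about 15% wider; the sample size does not change.

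**Optional and separate.** Replace single-step Bonferroni with Holm and keep the sample size based on 0.025. State in advance which interval goes with which step, for example that the 95% interval accompanies the 97.5% interval for a comparison tested at the second step. The costs are that one comparison's threshold then depends on the other's p value, and that a 97.5% interval may include no effect beside a second-step rejection.

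Both the Bonferroni rule and the interval level stand in the protocol, so either change means amending the protocol and the analysis plan with a documented rationale. This is best done before enrolment; the trial period is estimated to begin in September 2026.

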### Primary analysis of the secondary outcomes at 6 weeks

For continuous secondary outcomes at 6 weeks, we will use linear models or linear mixed-effects models. All models will include site and treatment group as fixed effects. For the MCSQ, CS-VAS and LCQ measured at three timepoints (baseline, 2 weeks and 6 weeks), we will include participant-level intercept as a random effect, and time and the interaction between treatment and time as fixed effects.

We will estimate marginal means (95% CI) at each timepoint. Between-group differences in mean changes from baseline at 6 weeks (95% CI) will be calculated using post hoc contrasts based on the model. Handling of missing data will follow the same approach as the primary outcome.

For secondary outcomes, p values for the treatment effect at week 6 will be reported at the conventional two-sided 0.05 level without adjustment for multiple comparisons. While the trial is powered for and will focus on inferential testing of the primary outcome of 24-hour cough frequency, we recognise that some secondary outcomes may better reflect patient-important benefits. Accordingly, interpretation of the trial findings will consider the overall pattern and consistency of effects across primary and secondary outcomes at 6 weeks.

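### The random-intercept model for MCSQ, CS-VAS and LCQ assumes equal correlation between all visits; under plausible patterns the standard error of the week-6 change contrast would be too small

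*Protocol article*

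**What the plan says.** Under Primary analysis of the secondary outcomes at 6 weeks, the protocol article models MCSQ, CS-VAS and LCQ with all three visits (baseline, week 2, week 6) in the response. Fixed effects are site, treatment group, and "time and the interaction between treatment and time as fixed effects". For the within-participant structure it says "we will include participant-level intercept as a random effect". It names no random slope, residual covariance, visit-specific variance or robust standard error.

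The estimate is then defined: "Between-group differences in mean changes from baseline at 6 weeks (95% CI) will be calculated using post hoc contrasts based on the model". P values are "reported at the conventional two-sided 0.05 level without adjustment for multiple comparisons". The same section adds that some secondary outcomes may reflect patient benefit better than cough frequency does, and that interpretation will weigh consistency across primary and secondary outcomes. The per-protocol analysis (Testing the impact of protocol adherence) reuses the same mixed model.

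**The concern.** A random intercept with independent, equal-variance residuals forces the same correlation on baseline–week 2, baseline–week 6 and week 2–week 6. The reported contrast uses only one of these pairs, baseline–week 6, which is the longest interval.

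The design gives a reason to doubt equal correlation. Every participant starts morphine or pregabalin after baseline, so individual response to treatment is present at weeks 2 and 6 but not at baseline. That tends to lower both correlations with baseline relative to week 2–week 6. Pregabalin is titrated over two weeks and CCT runs to week 6, so response may still be developing after week 2, which would lower the baseline–week 6 correlation further.

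At stake is whether the nominal 95% intervals and 5% tests for three scales, each used for two comparisons, have the coverage and error rate they claim.

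**Working it through.** **The plan's own figure.** The article gives no figure for these models. Its one computed design figure is the primary-outcome sample size: "a total sample size of 124 participants (62 per intervention comparison) will provide 80% power at a two-sided alpha of 0.025". This reproduces. The standardised effect is 0.357/0.6 = 0.595; a two-sample t-test at two-sided 0.025 and 80% power needs 54.97, so 55 per arm; 55/0.9 = 61.1, so 62 per arm and 124 in all. It does not bear on this point, except that 62 × 0.9 = 55.8 gives the 56 evaluable participants per arm used in the simulation below.

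**Formula.** Let V02, V06 and V26 be the variances of a participant's change between baseline and week 2, baseline and week 6, and week 2 and week 6, with V = s₁² + s₂² − 2·r·s₁·s₂ for each pair. Time is taken as categorical, because marginal means are planned at each timepoint. With complete data:

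- The estimate is the between-group difference in mean change, whatever covariance is fitted. Its true variance is governed by V06.
- The random-intercept model values that change at twice its residual variance, which converges to (V02 + V06 + V26)/3.
- Model SE / true SE = √[((V02 + V06 + V26)/3) / V06].
- Actual two-sided error at nominal 5% = 2·[1 − Φ(1.96 × ratio)].

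With equal SDs the ratio is below 1 exactly when r06 is below the average of r02 and r26. That happens when r06 is the lowest of the three, and also when the two correlations with baseline are equal and lower than r26.

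**Results, SDs all 1.** The correlations are assumptions; the documents state none.

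| r02 / r06 / r26 | V02 / V06 / V26 | SE ratio | Type I error |
|---|---|---|---|
| .6/.6/.6 (compound symmetry) | 0.8/0.8/0.8 | 1.000 | 5.0% |
| .6/.6/.7 | 0.8/0.8/0.6 | 0.957 | 6.1% |
| .5/.5/.7 | 1.0/1.0/0.6 | 0.931 | 6.8% |
| .7/.6/.7 | 0.6/0.8/0.6 | 0.913 | 7.4% |
| .6/.5/.7 | 0.8/1.0/0.6 | 0.894 | 8.0% |
| .5/.4/.7 | 1.0/1.2/0.6 | 0.882 | 8.4% |
| .7/.5/.7 | 0.6/1.0/0.6 | 0.856 | 9.3% |
| .8/.512/.64 (decay of 0.8 per 2 weeks) | 0.4/0.976/0.72 | 0.846 | 9.7% |
| .5/.6/.5 (reversed) | 1.0/0.8/1.0 | 1.080 | 3.4% |

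Worked example, .6/.5/.7: mean (0.8 + 1.0 + 0.6)/3 = 0.8; √(0.8/1.0) = 0.894; 2·[1 − Φ(1.752)] = 8.0%.

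**Unequal SDs.** Steadily rising or falling SDs barely move these ratios. The lowest found was 0.838 (SDs 1.2/1.1/1.0 with the decay pattern), giving 10.1%. Rising variance alone is not the cause: SDs 20/25/27 with all correlations 0.6 give 425, 481 and 544, mean 483.3, and √(483.3/481) = 1.00. With the same SDs and correlations .5/.4/.7 the variances are 525, 697 and 409, mean 543.7, ratio 0.883, type I error 8.3%; there the correlations do the work. A week-2 SD clearly above both others (1/1.3/1) moves the ratio to between 0.94 and 1.13 over the non-reversed patterns, so the direction can turn.

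**Simulation** (20,000 trials per pattern, 56 per arm, complete data, no treatment effect). Rejection with the random-intercept variance: 5.1% under compound symmetry, 7.0% (.5/.5/.7), 7.6% (.7/.6/.7), 8.3% (.6/.5/.7 with SDs 1/1.1/1.2), 9.2% (.7/.5/.7) and 3.4% (.5/.6/.5). Using the variance of the week-6 change itself, which is what an unstructured covariance uses with complete data, rejection was 4.6% to 5.2% in every pattern.

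**The case against.** The article does not say that the random intercept is the only structure. A residual covariance or robust standard errors could sit alongside it, and the analysis plan in online supplemental file 5, which is not shown, may add one. That is possible, but the article does name a structure for within-participant correlation, and its natural reading is that the intercept stands alone. The point concerns the model as stated.

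The size rests on assumed correlations. This stands in full: a reader might infer that the intervals and p values for these scales are certain to be anti-conservative, and the documents do not support that. Under compound symmetry there is no error, and some patterns give a conservative test. Nor do the documents support the inference that greater spread at week 6 produces the problem; the calculation above shows that it does not by itself.

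The calculations use complete data, whereas the plan imputes missing outcomes and expects 10% dropout. The error rates were not computed under that procedure. Imputation would not remove the mechanism, however, because the within-imputation variance still comes from the same model.

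Finally, a random intercept for three visits is a recognised choice, the trial's inferential focus is the primary outcome, and the secondary p values are openly unadjusted. This limits the consequence. It does not make a stated 95% interval accurate. The normality and homoscedasticity checks are described for the primary outcome's single-timepoint model and do not test equal correlation.

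**Conclusion.** The point holds as a conditional risk that is cheap to remove. If the baseline–week 6 correlation is below the average of the other two, as the treatment schedule makes plausible, the standard error of the week-6 contrast is about 4% to 16% too small over the patterns tried. Type I error is then about 6% to 10% instead of 5%, and nominal 95% intervals cover about 90% to 94%. These figures assume complete data, categorical time and ordinary independent residuals, with correlations that the documents do not supply.

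The effect is confined to the standard errors, intervals and p values of MCSQ, CS-VAS and LCQ at week 6, and to the per-protocol reuse of the model. A reader might extend it to the treatment-effect estimates or to cough frequency. Neither follows: the complete-data point estimate is the same under either covariance, and the primary outcome uses a linear model at one timepoint.

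**What to change.** In Primary analysis of the secondary outcomes at 6 weeks, and in the per-protocol reuse under Testing the impact of protocol adherence, replace the random intercept with an unstructured 3×3 within-participant covariance and Kenward-Roger degrees of freedom. State the fallback in advance: if that model does not converge, keep the random intercept and report robust (sandwich) standard errors.

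The unstructured model is valid whether or not compound symmetry holds. It has six covariance parameters instead of two, which 124 participants with three visits estimate easily. The cost is those four extra parameters and a negligible loss of precision if compound symmetry is true. No data collection or sample size changes.
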